##### Sample size

The sample-size calculation is based on change in RDQ at 3 months after onset of LBP. It is recommended that a change of 2 to 3 points on the RDQ should be considered the minimum clinically important change [48]. To allow for the cluster randomisation by PHCC, we assume an intraclass correlation coefficient of 0.1 [49] and a minimum average number of individuals sampled per PHCC of 25. In order to detect a difference of 2.5 points between the two intervention arms with a standard deviation of 5.7 [48,50], an alpha error of 0.05, a beta error of 0.10, and a 20% dropout rate, a sample size of 932 subjects was required, 466 subjects per intervention arm. Therefore, the total number of PHCCs is 38 (19 in each group).

##### Statistical Analysis

The effectiveness of the intervention will be analysed in accordance with CONSORT guidelines, extended to a cluster randomised trial. The analysis will be carried out according to the intention-to-treat principle. Cost, outcomes and use of resources will be reported as mean values with standard deviations for each intervention arm. Comparisons will be done between arms on characteristics of the study population. Mean differences between groups in cost, outcomes and resources, and 95% confidence intervals were calculated. If cost data do not conform to the assumptions for standard statistical tests, the non-parametric bootstrap method will be performed [51].

To address potential biases due to incomplete follow-up, we will analyse patients with complete data at all time points and those with data at any time point, using the multiple imputation approaches to replace missing values. Bias due to non-response will be assessed at each follow-up.

The temporal horizon of the study is 3 months because this is the time of change to a chronic stage and 12 months to evaluate the outcomes at long term.

The discount rate will be 3% [52] that is closest to the actual discount rate.

To establish an important change in individuals, we will contrast the distributions of changes in all the questionnaires and in each assessment, in individuals who change to chronic state and those who do not [48]. We will do the same between those individuals who return to work and those who do not. We will compare individual change scores to the standard error of measurement (SEM).

To detect changes in groups, the intervention effect will be calculated through the effect size for each questionnaire and at each assessment. Effect size will be calculated following the method of Kazis et al [53].

We will evaluate responsiveness of each scale by standardized response mean (SRM) [54] and receiver-operating characteristic method (ROC curve). Since the unit of randomisation is the PHCC, we will use a regression analysis of individual level data using methods for clustered data [55].

To adjust comparisons and to account for cluster randomisation, multilevel linear regression analyses on repeated measures on each of the outcome scales will be used to assess the effect of intervention and to investigate the factors that influence each of the outcome scales at each time point. The possible association between intervention and time will be studied. The PHCC and the individual will be considered as random effects and intervention and time as fixed effects.

The incremental cost-effectiveness ratios were calculated as the difference in mean costs between the MBEGI and the usual care divided by the difference in mean effect, measured in natural unit, between MBEGI and the usual care.

Utilities will be calculated from the SF-12 scores with the corresponding Oxford University algorithm. The QALY will be calculated using these utilities, adjusted by time. The incremental cost-utility ratio will be calculated by dividing the difference in mean total costs between the MBEGI and the usual care by the difference in QALYs [56,57].

To determine the uncertainty surrounding these ratios, 95% confidence intervals for cost-effectiveness ratios will be calculated by the non-parametric bootstrap method [51].

Acceptability curves will be use to determine the probability that the MBEGI will be cost effective compared with usual clinical care at different values of the maximum acceptable ratio.

A deterministic sensitivity analysis will be performed to assess the robustness of the results [58]. The sickness days, GP visits and the number of medications will be measured to assess the impact on costs and cost-effectiveness. The discount rate will be 1% and 5%.

Confidence intervals around point estimates will be reported. The results will be presented in a disaggregated as well as aggregated form.

The significance level of all models will be set at 5%. The SPSS statistical package for Windows, version 19 (SPSS Inc., Chicago, IL) and the Stata/SE version 11·1 for Windows (StataCorp LP) will be used for statistical analysis.

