### Randomisation

In this study a cluster design is used because the intervention is delivered to groups. To minimise contamination, the unit of randomisation will be the PHCC. Those PHCCs who agree to participate will be randomly allocated to control or intervention groups by a random sequence generated by a computer programme in blocks of random size and prepared before recruitment of the PHCC by an independent statistician who will be blinded to the PHCC identity. The blocking factor was a randomly selected even number (i.e., 4, 6, or 8) and will vary as the recruitment continues. GP or nurses will be informed about their allocation after giving final consent to participation.

To minimise imbalance across intervention groups, randomisation was stratified by percentage of immigrants from developing countries registered in each district. We consider two strata, less than and more than 15% immigrants. This variable is taken as a proxy of socioeconomic level.

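### Read as random intercepts, the stated random effects would carry none of the assumed ICC of 0.1 into an intervention-by-time test of the 3-month RDQ change

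*Protocol article*

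**What the plan says.** All places are in the protocol article, under Methods/Design.

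- **Randomisation:** centres are randomised. "To minimise contamination, the unit of randomisation will be the PHCC".
- **Sample size:** "The sample-size calculation is based on change in RDQ at 3 months after onset of LBP". For clustering, "we assume an intraclass correlation coefficient of 0.1 [49] and a minimum average number of individuals sampled per PHCC of 25". The target is set as follows: "In order to detect a difference of 2.5 points between the two intervention arms with a standard deviation of 5.7". With 90% power and 20% dropout this leads to 466 patients per arm and 19 PHCCs per arm.
- **Data collection and information sources:** assessments are at the first visit and at 3, 6 and 12 months.
- **Statistical Analysis:** a multilevel linear regression on the repeated measures is meant to deal with the cluster randomisation. Its structure is: "The PHCC and the individual will be considered as random effects and intervention and time as fixed effects". On change over time: "The possible association between intervention and time will be studied". The section also makes a general commitment to clustered-data methods.

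No PHCC-by-time random effect is named. The section does not say which contrast tests the 3-month effect, or whether the first visit is an outcome or a covariate. The Ethical aspects section refers to a separate effectiveness protocol for more detail on the effectiveness analysis.

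**The concern.** The trial is sized on a change, and the sizing attaches an ICC of 0.1 to it. Time enters the analysis model only as a fixed effect, so the natural reading is one constant effect per PHCC and one per patient. Constant effects subtract out of any within-patient change. An arm difference in change taken from this model therefore has a standard error with no between-PHCC part, although whole PHCCs were randomised.

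Between-PHCC variation in change is plausible here. The Discussion expects some variability in how local professionals apply the guideline, and the intervention is delivered in groups of up to 12. If such variation exists and the change contrast is used for inference, the confidence interval is too narrow and the 5% level is not kept. The same model is planned for every outcome scale, so the issue is not confined to RDQ.

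**Working it through.** **1. Reproduce the sample size.** Inputs from the Sample size section: difference 2.5, SD 5.7, alpha 0.05 (taken as two-sided), power 90%, ICC 0.1, 25 per PHCC, dropout 20%.

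- Per arm without clustering: 2 × (1.96 + 1.2816)² × 5.7² / 2.5² = 109.2
- Design effect: 1 + (25 − 1) × 0.1 = 3.4
- 109.2 × 3.4 / 0.8 = 464 (468 if 109.2 is first rounded up to 110), against 466 stated.

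The figure reproduces, so the document does put a design effect of 3.4 on the 3-month change.

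**2. What the model implies for change.** Write the plain reading as Y(PHCC j, patient i, visit t) = fixed effects of arm, time and arm-by-time + b(j) + u(ij) + e(ijt). The change from first visit to 3 months contains e(ij,3) − e(ij,0), while b(j) and u(ij) cancel. The implied ICC of change is 0, against 0.1 in the sizing. In a two-visit mixed model fitted to simulated data, the standard error of the interaction equalled that of an independent-samples comparison of change scores (both 0.556148), against 0.687 from PHCC means.

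**3. Size at the document's ICC.** Take 19 PHCCs per arm and 25 × 0.8 = 20 completers each, so 380 per arm.

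- SE ignoring clustering of change: √(2 × 5.7² / 380) = 0.414
- Design effect: 1 + 19 × 0.1 = 2.9
- SE with clustering: 0.414 × √2.9 = 0.704
- True type I error: 2 × (1 − Φ(1.96 / √2.9)) = 25%

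With 25 analysed per PHCC the design effect is 3.4, the SEs are 0.370 and 0.682, and the error is 29%.

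**4. Smaller ICC of change** (assumed range, 20 per PHCC, same formula):

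| ICC of change | Design effect | Type I error |
|---|---|---|
| 0.10 | 2.90 | 25% |
| 0.05 | 1.95 | 16% |
| 0.02 | 1.38 | 9.5% |
| 0.01 | 1.19 | 7.2% |
| 0 | 1.00 | 5% |

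**5. Other contrasts from the same model.** Simulation: 38 PHCCs, 20 patients each, four visits, 4,000 runs, ICC of change 0.1. Assumptions not in the documents: baseline ICC 0.05, between-patient variance 12, equal cluster sizes, and PHCC-by-time effects either independent or shared across follow-up visits.

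| Test | Independent | Shared |
|---|---|---|
| Change to 3 months (interaction) | 24.1% | 26.7% |
| Arm difference at 3 months | 12.7% | 8.5% |
| Arm difference averaged over visits | 4.9% | 5.2% |
| PHCC-level t-test of change | 5.0% | 5.1% |

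If only the follow-up visits are outcomes (separate simulation, total ICC 0.1), the error is 5.7%, 6.6% and 8.6% at a PHCC autocorrelation of 1, 0.8 and 0.5.

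**6. Power of a valid test.** SE 0.704, difference 2.5, 38 − 2 = 36 degrees of freedom, noncentral t: 93%.

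**The case against.** A reader might infer that the protocol tests the 3-month RDQ change as if patients were independent. The text does not go that far, and several points on the other side stand:

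- That the random effects are intercepts only is an inference. The article neither states it nor excludes a PHCC-by-time term.
- The intervention-by-time association is only to be studied. No sentence makes it the test of the 3-month effect. The visit-averaged arm effect keeps 5%.
- Baseline handling is open. If the modelled outcome were the change score itself, the PHCC effect would sit on change and the problem would vanish. If only follow-up visits were outcomes, inflation would be small.
- The Sample size section does not say that its ICC was estimated on change scores. One psychologist and one physiotherapist serve all PHCCs, which may limit between-centre variation in the intervention arm.
- Exact cancellation needs balanced data. With missing visits it is approximate.

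Two further defences are weaker. The commitment to clustered-data methods states an aim, and cluster-robust inference would meet it. However, the random effects are the only means that the article specifies, and they do not protect a change contrast. The separate effectiveness protocol may say more, but this article chose to state the structure; if the two differ, they need reconciling. The visit-averaged effect, though valid, would include the first visit if that is an outcome, and is not the 3-month change on which the trial was sized.

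**Conclusion.** The point holds conditionally. On the plain reading, with the first visit among the repeated measures, the model carries none of the sized ICC into the intervention-by-time contrast. If that contrast decides the 3-month effect, the nominal 5% becomes about 25% at the document's ICC with 20 completers per PHCC, and roughly 7% to 16% for an ICC of change of 0.01 to 0.05. The arm difference at 3 months is partly protected (about 9% to 13%) and the visit average fully (about 5%). What the article gets wrong is stating a random-effects structure that does not match its sizing quantity while leaving the deciding contrast open. It does not commit itself to an analysis that ignores clustering. The sample size is sound.

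**What to change.** In the Statistical Analysis section:

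1. Name the arm difference in RDQ at 3 months, as change or baseline-adjusted value, as the test that matches the sample size.
2. Either add a PHCC-by-time random effect beside the PHCC and individual effects, or model the 3-month value (baseline-adjusted) or change with a PHCC random effect. The second is simpler for the main contrast, because it needs no assumption about how PHCC effects correlate across visits.
3. Use between-PHCC degrees of freedom (about 36).
4. Apply the same structure to the other outcome scales.

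The cost is a few words and one variance component, with no new patients or data. Intervals widen: at an ICC of change of 0.1 the 95% half-width goes from 1.96 × 0.414 = 0.81 to 2.03 × 0.704 = 1.43 points. Power at 38 PHCCs stays about 93%, above the planned 90%, so N need not change.

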##### Utility measures

The primary utility measure of the study is quality adjusted life years (QALYs), and will be calculated from the SF-12 scores (scale 0-100; lower score indicates poorer quality of life) [32].

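### Incremental QALYs are set out as a between-arm difference with no adjustment for baseline SF-12 utility, so part of any baseline imbalance carries into the cost-utility ratio

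*Protocol article*

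**What the plan says.** Under Utility measures, the article states: "The primary utility measure of the study is quality adjusted life years (QALYs), and will be calculated from the SF-12 scores". Under Statistical Analysis, it derives utilities from the SF-12 and adds: "The QALY will be calculated using these utilities, adjusted by time". The cost-utility ratio is obtained by "dividing the difference in mean total costs between the MBEGI and the usual care by the difference in QALYs". Uncertainty comes from a non-parametric bootstrap and acceptability curves.

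The same section plans regression on individual data with methods for clustered data. It then describes multilevel repeated-measures models, introduced as the means of adjusting comparisons, for each outcome scale. Intervention and time are the fixed effects; centre and individual are the random effects. The arms are also to be compared on patient characteristics. The deterministic sensitivity analysis varies sickness days, GP visits, number of medications and the discount rate.

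Data collection and information sources places outcome assessments at the first visit and at 3, 6 and 12 months. Randomisation says that GPs and nurses learn their allocation once they have agreed to take part. Study population says that the GP or nurse, or a search of clinical records, then identifies eligible patients.

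**The concern.** The only adjustment named for the QALY is by time, which is weighting by duration and not adjustment for a covariate. Nothing in the article puts baseline utility into the QALY difference, the ratio, the bootstrap or the sensitivity analysis.

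Baseline utility matters in two ways. It is the starting point of the utility curve, so it is part of each patient's QALY. It also predicts utility at later visits. A difference between arms at the first visit therefore shows up as a QALY difference even if the intervention does nothing.

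Such a difference is plausible here. Only 38 centres are randomised, stratified on immigrant percentage alone, and patients are identified by staff who already know the arm. At stake is the denominator of the cost-utility ratio, where a small shift can change the ratio a good deal.

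**Working it through.** **The plan's own figure.** The article gives no sample-size or precision figure for QALYs. Its sample size rests on the RDQ: "In order to detect a difference of 2.5 points between the two intervention arms with a standard deviation of 5.7", "an alpha error of 0.05, a beta error of 0.10, and a 20% dropout rate", and "we assume an intraclass correlation coefficient of 0.1" with 25 patients per centre.
- Per arm before inflation (two-sided): 2 × [5.7 × (1.960 + 1.282) / 2.5]² = 109.24.
- Design effect: 1 + (25 − 1) × 0.1 = 3.4.
- With dropout: 109.24 × 3.4 / 0.80 = 464.3 per arm, or 930 in total. Rounding 109.24 up to 110 first gives 936.

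The stated 932 is reproduced closely, so 466 per arm and 932/38 = 24.5 per centre are used below.

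**Inputs not in the article (assumed).** Utility SD 0.08 to 0.15; utility ICC 0.01 to 0.10; correlation r between baseline and each later utility 0.3 to 0.7, with equal SD at all visits; linear interpolation, with the first visit taken as time zero.

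**QALY weights.** Visits at 0, 0.25, 0.5 and 1 year give:
- baseline: 0.25/2 = 0.125
- 3 months: 0.5/2 = 0.25
- 6 months: (1 − 0.25)/2 = 0.375
- 12 months: 0.5/2 = 0.25

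**Carry-over at 12 months.** The share of a baseline difference that reaches the incremental QALY is 0.125 + 0.875r.

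| r | Share | Shift from a 0.02 imbalance |
|---|---|---|
| 0.3 | 0.3875 | 0.0078 |
| 0.5 | 0.5625 | 0.0112 |
| 0.7 | 0.7375 | 0.0147 |

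At the 3-month horizon the weights are 0.125 and 0.125, so the shift is 0.02 × (0.125 + 0.125r), or 0.0033 to 0.0043.

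The follow-up visits are timed from onset of pain, so the first interval may be shorter than three months and the baseline weight below 0.125. In the limit of zero weight the share is r itself, 30% to 70% per year of follow-up, so the conclusion does not depend on 0.125.

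**Chance imbalance.** SE of the baseline difference = SD × √[(2/466) × (1 + 23.5 × ICC)].
- SD 0.08, ICC 0.01: 0.0058; 1.96 SE = 0.011.
- SD 0.15, ICC 0.10: 0.0180; 1.96 SE = 0.035.

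An imbalance of one SE carries between 0.3875 × 0.0058 = 0.0023 and 0.7375 × 0.0180 = 0.0133 QALY into the result.

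**Simulation check.** 38 centres of 25, SD 0.12, ICC 0.05, r = 0.5, no true effect, 1,500 runs.

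| Built-in baseline imbalance | Crude QALY difference, mean (SD) | Baseline-adjusted, mean (SD) |
|---|---|---|
| 0 | −0.0002 (0.0071) | 0.0001 (0.0035) |
| 0.02 | 0.0110 (0.0076) | −0.0001 (0.0035) |

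The crude shift agrees with 0.5625 × 0.02 = 0.0113. The halving of the SD is a favourable case, because in this model the centre effect reaches follow-up only through baseline. Removal of the shift is complete for the same kind of reason: the imbalance acts only through baseline utility. The simulation supports the direction of the gain, not a firm figure for it.

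**The case against.** The strongest reply is that this is silence rather than error. The article never calls the difference unadjusted, its ratio is the textbook definition, and covariates are often left to a fuller plan. The sentence on regression for clustered data is not limited to particular outcomes, and the SF-12 could count as one of the outcome scales. This is fair as far as it goes: that the difference is unadjusted is an inference from the formula, and so is a first-visit SF-12, since the article does not name the instruments used at each visit. But this article is the protocol of the economic evaluation and writes the estimator out. A multilevel model of the SF-12 scale would show a baseline difference without removing it from the QALY or the ratio.

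A reader might also infer that a baseline imbalance passes one-for-one into the QALY. It does not: the carry-over is partial, and at 3 months it is small in absolute terms.

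A reader might infer that chance imbalance biases the result. In expectation it does not; it is sampling noise that a suitable bootstrap would reflect. Only differential recruitment would bias the estimate. The article gives a route for it, because staff know the centre's arm, but no evidence that it happens. Blinding places patient consent before allocation, which protects little when the arm is fixed by the centre.

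Finally, a reader might extend the point to costs. No corresponding defect in the cost difference has been shown.

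**Conclusion.** The point holds in a limited form. As written, the incremental QALY is a between-arm difference without baseline utility as a covariate, and the planned multilevel adjustment is not said to reach it. Under linear interpolation and correlations of 0.3 to 0.7, about 39% to 74% of a baseline utility imbalance carries into the 12-month incremental QALY, or about 0.008 to 0.015 for an imbalance of 0.02. Imbalances of 0.011 to 0.035 lie within 1.96 SE of zero by chance, depending on the assumed SD and ICC.

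It does not follow that the cost-utility conclusion would be reversed. The article states neither an expected QALY gain nor a fixed value for the maximum acceptable ratio, so no such claim and no monetary size can be derived from it. The supported conclusion is that the plan accepts avoidable noise, and exposure to recruitment bias, in its primary utility measure.

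**What to change.** State in the Statistical Analysis section that incremental QALYs, at 3 and 12 months, will be estimated by regressing patient QALYs on arm, baseline SF-12 utility and the randomisation stratum (immigrant percentage below or above 15%), allowing for clustering by centre. Use that estimate as the denominator of the cost-utility ratio, refit the regression in every bootstrap resample, and build the acceptability curve from the same resamples. Report the unadjusted difference as a sensitivity analysis. State explicitly that the SF-12 is completed at the first visit.

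This is a change of analysis wording. Sample size and data collection are unchanged, provided the first-visit assessment includes the SF-12 as it appears to. Adjustment removes only the imbalance that baseline utility predicts, so recruitment differences in other prognostic factors would remain.

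### No step named for costs, cost-effectiveness ratios or acceptability curves accounts for PHCC clustering, and the uncertainty is placed on the ratio itself

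*Protocol article*

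**What the plan says.** Under Randomisation, the protocol article states that "the unit of randomisation will be the PHCC", with two strata defined by the percentage of immigrants. Under Sample size, the clusters enter the calculation: "we assume an intraclass correlation coefficient of 0.1", with "a minimum average number of individuals sampled per PHCC of 25". The result is 932 patients in 38 PHCCs, 19 per arm.

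Under Statistical Analysis, clustering appears twice. A general sentence promises individual-level regression with methods suited to clustered data; it directly follows the text on the responsiveness of the scales. Then "multilevel linear regression analyses on repeated measures on each of the outcome scales will be used to assess the effect of intervention", with PHCC and individual as random effects. Costs and QALYs are not named in either place.

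The economic results are described differently. Costs are compared through mean differences with 95% intervals, and "If cost data do not conform to the assumptions for standard statistical tests, the non-parametric bootstrap method will be performed". The ICER and the cost-utility ratio are each defined as one difference in arm means divided by another. For their uncertainty, "95% confidence intervals for cost-effectiveness ratios will be calculated by the non-parametric bootstrap method". Acceptability curves are planned, but the article does not say how they are generated. Resampling unit, strata, pairing of cost with effect, and type of interval are not stated. Net monetary benefit is not mentioned.

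**The concern.** The bootstrap is introduced to deal with the shape of cost data, not with clustering. It is then carried over to the ratios, while the model that handles the clusters is reserved for the questionnaires. Followed as written, the economic analysis contains no step that respects the unit of randomisation. If the bootstrap is run on patients, the standard errors leave out the between-centre component that the sample size was built to absorb.

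A second, separate matter is the interval on the ratio. The Discussion expects better outcomes and lower costs, which is where ratios are hardest to read. A negative ratio can mean that MBEGI dominates or that it is dominated, and sorting replicates mixes the two.

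These intervals and curves are the main results of an economic evaluation meant to inform adoption in primary care.

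**Working it through.** **1. Reproduce the plan's sample size.** Inputs, all from Sample size: "In order to detect a difference of 2.5 points between the two intervention arms", "with a standard deviation of 5.7", alpha 0.05 (taken as two-sided, which the article does not state), power 0.90, ICC 0.1, 25 per PHCC, 20% dropout.

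- Per arm, unclustered: 2 × (5.7 × (1.960 + 1.282) / 2.5)² = 109.2
- Design effect: 1 + (25 − 1) × 0.1 = 3.4
- Per arm, clustered: 109.2 × 3.4 = 371.4
- After dropout: 371.4 / 0.80 = 464.3 per arm, 928.6 in total (936 if rounded up at each step)

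The stated 932 lies between these, so the design effect of 3.4 is the protocol's own.

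**2. Effect of resampling patients instead of PHCCs.** With design effect DE = 1 + (m − 1) × ICC, the standard error is understated by a factor √DE. The interval has 1/√DE of its correct width, and nominal 95% coverage becomes 2Φ(1.96/√DE) − 1. With 20% dropout, m = 932 × 0.8 / 38 = 19.6.

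| ICC | m | DE | Relative width | Coverage |
|---|---|---|---|---|
| 0.1 (protocol, for RDQ) | 25 | 3.40 | 0.54 | 71% |
| 0.1 (protocol, for RDQ) | 19.6 | 2.86 | 0.59 | 75% |
| 0.05 (assumed) | 25 | 2.20 | 0.67 | 81% |
| 0.02 (assumed) | 25 | 1.48 | 0.82 | 89% |
| 0.01 (assumed) | 25 | 1.24 | 0.90 | 92% |

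For the first row, √3.4 = 1.84 and 1.96/1.84 = 1.06, which gives 71%.

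**3. Simulation check.** Setting: a mean difference, 19 PHCCs per arm, 25 patients each, normal data, 600 trials with 400 bootstrap samples each, percentile intervals. At ICC 0.1 the patient bootstrap covered 69% and the PHCC bootstrap 91%, with PHCC intervals 1.77 times as wide. At ICC 0.05 the figures were 83% and 93.5%; at ICC 0.01, 90% and 91.5%. The Monte Carlo standard error is about 1 point for coverage near 92%. The simple PHCC percentile bootstrap therefore falls slightly short itself with 19 clusters per arm.

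**4. Acceptability curve.** If the curve is drawn from patient-level replicates, a true probability p is read as Φ(z_p × √DE). For p = 0.80 (z = 0.842) and m = 25, the reading is 0.83 at ICC 0.01, 0.89 at ICC 0.05 and 0.94 at ICC 0.1.

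**5. The ratio.** Illustration with independent normal draws, the cost difference 1 SE above zero, in SE units, using percentile limits (an assumption, since the article names no interval type):

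| Effect difference | Negative denominators | Ratio interval | Median |
|---|---|---|---|
| 1 SE | 16% | −10.7 to 11.9 | 0.6 |
| 2 SE | 2.3% | −1.1 to 3.8 | 0.5 |
| 3.24 SE | 0.05% | −0.3 to 1.3 | 0.3 |

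The last row is the RDQ effect for which the trial is powered (1.960 + 1.282 = 3.24). The QALY difference has no such calculation behind it and may lie in the upper rows.

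Ordering also fails within the dominant quadrant. Saving €1,000 with a gain of 0.1 QALY gives −10,000, while the same saving with only 0.01 QALY gives −100,000, so the worse result has the more negative ratio. For the RDQ, where lower is better, the raw-difference ratio also carries the opposite sign meaning from the QALY ratio.

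**The case against.** A reader might infer that the plan prescribes a patient-level bootstrap that ignores the PHCCs and so yields intervals that are far too narrow. The article does not support that. It names no resampling unit and no interval type, and a bootstrap of PHCCs is also non-parametric. A condensed article may leave such detail to a fuller plan, and the general sentence on clustered regression could be read to include costs.

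The size is also conditional. The ICC of 0.1 belongs to a calculation on RDQ change at 3 months. At an ICC of 0.01 the interval is only about 10% too narrow. The cost bootstrap is itself conditional on failed assumptions, and the acceptability curves are not tied to it. Those curves, being shown across thresholds, already answer part of the quadrant problem, and at the powered RDQ effect almost no denominators change sign.

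Much of this stands, and it limits how strongly the point can be put. It does not remove the point. The general sentence concerns regression, whereas the ICER and cost-utility ratio are defined as ratios of raw mean differences with a bootstrap, not as regression output. The article refers readers to the companion protocol for the intervention, adherence and the effectiveness analysis, not for the economic analysis. The interval on the ratio is written in the text and is not a matter of silence. The curves help only if their replicates respect the clusters.

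**Conclusion.** The concern holds in a conditional form. The design and sample size account for the PHCC; no step named for cost differences, ICERs, cost-utility ratios or acceptability curves does. If patients are resampled, nominal 95% coverage lies between about 71% and 92% over ICCs from 0.1 down to 0.01 at 25 patients per PHCC. Only the value 0.1 comes from the article, and there it serves the RDQ; the lower values are assumptions. These figures describe a mean difference in cost or effect with equal cluster sizes. It cannot be said from the article that the intervals will be far too narrow, because neither the resampling unit nor the ICC for costs and QALYs is given.

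The interval on the ratio is a distinct weakness. It affects interpretation, not width, and matters most for the QALY ratio, for which the trial was not sized.

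**What to change.** State that uncertainty for costs, QALYs, ICERs, cost-utility ratios and acceptability curves comes from one of two methods:

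- a bootstrap that resamples PHCCs within arm and immigrant stratum, keeps each patient's cost-effect pair together, and includes a small-sample correction for 19 clusters per arm (resampling within strata makes the cells smaller still, so the correction should be named in advance); or
- a bivariate multilevel model for cost and effect with a PHCC random effect.

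Draw the acceptability curves from the same replicates or model. Report incremental net monetary benefit with its 95% interval over a range of thresholds, together with the cost-effectiveness plane, and give the ICER as a point estimate.

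The cost is a change of wording, modest programming and wider intervals. No new data are needed.
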